### Sample size

One hundred and fifty-four patients will be recruited in total, 77 per trial arm. This sample size will provide adequate power to detect a standardised mean difference of 0.5 (medium magnitude) in the primary outcome between the treatment and control groups at the end of intervention assessment (5% significance, 80% power), assuming attrition of 20%. Using data from Vincent *et al*,^35^ this equates to between an 11.5-point and 15.8-point difference on each of the INQoL domains. While no information is currently available regarding clinically important differences for the INQoL, an effect size of this magnitude typically relates to a clinically important difference for health-related QoL instruments.^46^

### Recruitment

Participants will be recruited from MD clinics, MD-UK and MD registries. In MD clinics, consultants and physiotherapists will identify potentially eligible participants who will either be given an information pack consisting of an invitation letter, information sheet and reply slip to state their interest. MD-UK and MD registries will advertise the study and provide invitation packs. When someone states their interest, the RA will call them to provide further information, answer any questions and conduct screening. If they are eligible for the study (including medical confirmation from their health professional), then the participant will sign a consent form before being enrolled into the study.

## Methods: assignment of interventions

### Allocation

Randomisation will be conducted by an independent randomisation service at the UK Clinical Research Collaboration registered at the King’s Clinical Trials Unit. Randomisation will be at the level of the individual, using block randomisation with randomly varying block sizes stratified by recruiting centre. Allocation confirmation will be generated automatically and sent to unblinded research members, including the trial coordinator and clinical psychologist.

### Allocation concealment

A position of equipoise will be maintained, but blinding of the patients and therapist to the treatment condition will not be possible. The RA contacting participants and inputting data will be blind to group allocation to reduce the risk of introducing bias. To protect against unblinding, all follow-up questionnaires will be completed by participants on Bristol Online Survey (BOS) which is specifically designed for academic research and fully compliant with UK data protection law. All questionnaires will be identical for both arms and designed not to reveal treatment allocation. The trial statistician will be blind to treatment group when conducting the main data analysis.

## Methods: data collection, management and analysis

### Data collection methods

Baseline data will be collected prior to randomisation and consist of self-report questionnaires and objective assessments with the physiotherapist. Follow-up data (3, 6 and 9 weeks) include self-report questionnaires that will be completed remotely. At each follow-up point, participants will be emailed a link to BOS along with their unique identification number. If participants are unwilling or unable to complete all the questionnaires, they will be given the option of going through them on the phone or a reduced questionnaires pack with the primary outcomes (INQoL).

### Data management

All trial data will be stored in line with the Data Protection Act 1998 and in compliance with Good Clinical Practice and King’s College London data management procedures. Any identifying data will be anonymised through use of unique identification numbers separated from identifying data. Data will be entered onto password-protected trial databases either on a shared hard-drive accessible only to assigned team members or in a locked cabinet in a room only accessible to staff with designated access cards. All source documents will be retained for a period of 10 years following the end of the study.

### Statistical methods

Statistical analyses of the primary and secondary outcomes will be conducted after the database has been locked, with no interim analyses. All analyses will adopt the intention to treat principle. The main statistical analyses will estimate the difference in mean outcomes between patients randomised to ACT plus SMC and SMC alone at the primary endpoint of 9 weeks and at the two other postrandomisation time points. Group difference estimates, associated CIs and standardised effect sizes will be reported. Significance testing will be performed where the significance level will be 5% (two-sided). Sensitivity analyses will be used to assess the robustness of conclusions to missing outcome data using a pattern mixture model approach and to departures from randomised treatment in a per protocol analysis excluding those not receiving. Loss to follow-up, departures from randomised treatment and the prevalence of serious adverse events (SAEs) will be reported.

The primary outcome is the INQoL QoL score. Quality of life at all three postrandomisation time points (3, 6 and 9 weeks after randomisation) will be modelled simultaneously using a linear mixed-effects model. A random intercept will account for the non-independence of observations across individuals. Trial arm and indicator-coded time will be included as covariates along with arm by time interaction terms to allow the treatment effect to vary at each time point. In addition, included in the model will be the baseline level of the QoL score and a stratification indicator variable for centre. Missing data at follow-up assessments are allowed where at least one observation per participant is available under the missing at random assumption.

Secondary patient outcomes (3, 6 and 9 weeks after randomisation) relating to symptom severity and functioning (WSAS and HAQ-DI), distress (HADS), impression of change (PGIC) and putative mediators of the intervention (CAQ, AAQ-II and MAAS) will be analysed using linear mixed-effects models. Random effects for the intercept and time will be included in the model.

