### The selection of a guided self-help approach

The one comprehensive trial of a psychological intervention in MD^14^ tested the efficacy of a 16-session traditional cognitive behavioural therapy for improving fatigue. While results were encouraging, on both fatigue and secondary outcomes such as QoL and mood, for several reasons (including the time spent travelling), uptake was low, and a proportion (24%) struggled to achieve even a minimal level of adherence to the intervention. This suggests that issues, perhaps mobility difficulties and treatment length, may hinder face-to-face treatment options for many with MD. A further problem with the development and implementation of any new treatment concerns the resource limitations common to many health service providers, including the National Health Service (NHS) in the UK.

A practical solution to this problem could be the implementation of an intervention delivered remotely through online and computerised self-guided resources aided by telephone or video calls. Such methods of delivery are increasingly feasible given that the majority of UK households now have web access. In addition, recent systematic reviews suggest that promising results can be obtained from web-based interventions for adults with chronic illnesses and depression.^25–27^ Web-based interventions not only remove the burden of travel but also allow the completion of material at a convenient place, time and pace. Remotely delivered interventions can be a cost-effective approach for providing treatment, increasing its chances of wider implementation.

Given the potential benefits of using ACT within an MD population and taking into account potential barriers to participation, we developed, for this population, a brief self-guided intervention that can be supported remotely via email and telephone contact with a therapist. We assessed this in a preliminary multiple-baseline case series with seven participants.^28^ The results of this case series suggested that such an approach was practicable and acceptable, and that mood and QoL might respond to this treatment. Given this promising evaluation, we plan to conduct an RCT, to evaluate the efficacy of this intervention for improving QoL in people living with MD.

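### The per-protocol check on departures from treatment would drop people essentially from the ACT arm alone, so it is not a randomised comparison; a complier analysis should answer that question

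*Protocol article*

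**What the plan says.** The Statistical methods section opens with a general rule: "All analyses will adopt the intention to treat principle". The main analysis estimates the group difference at 9 weeks, and at 3 and 6 weeks, from a linear mixed model with baseline QoL and centre as covariates.

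Two sensitivity analyses follow. One concerns missing data: "Sensitivity analyses will be used to assess the robustness of conclusions to missing outcome data using a pattern mixture model approach". The other concerns treatment received: "departures from randomised treatment in a per protocol analysis excluding those not receiving". The second sentence stops without saying what is not received. Departures from randomised treatment will also be reported descriptively, but no other inferential method for them is named.

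Two other sections settle who could be a non-receiver. Under Standard medical care, SMC is the continuation of existing care without psychological therapy, and both arms get it. Under Acceptance and Commitment Therapy, the programme is four modules with audio files and five calls with the trial therapist.

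On the likely extent of non-receipt, the article gives only a figure from an earlier trial of 16-session cognitive behavioural therapy in muscle disease, where "a proportion (24%) struggled to achieve even a minimal level of adherence to the intervention".

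**The concern.** An SMC participant has no module or call to miss. A rule that excludes non-receivers therefore removes people from the ACT arm and leaves the SMC arm whole. The ACT side is then selected on behaviour after randomisation, while the SMC side still contains the people who would not have engaged had they been offered ACT. Any difference in prognosis between engagers and non-engagers enters the estimate as if it were a treatment effect.

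Such a difference is plausible on the article's own account. It suggests that mobility difficulties and treatment length may have hindered uptake and adherence in the earlier trial, and its Background calls physical disability a determinant of QoL. If engagers have the better prognosis, the per-protocol estimate leans towards ACT and could be read as confirming the primary result when it partly reflects selection.

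**Working it through.** **Sample size, reproduced first.** The article plans "One hundred and fifty-four patients will be recruited in total, 77 per trial arm", for "adequate power to detect a standardised mean difference of 0.5 (medium magnitude) in the primary outcome", with two-sided 5% significance, 80% power and 20% attrition. The normal approximation gives n = 2(1.960 + 0.842)²/0.5² = 63 per arm. Then 63/0.8 = 79 per arm, or 158 in total, within 3% of 154. (The t-test version gives 64, and 64 × 1.2 = 77 per arm, exactly 154.) With 77 × 0.8 = 61.6 completers per arm, power is 79%. The stated size therefore reproduces, and 61.6 per arm is used below.

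**Bias formula.** Let p be the fraction who would not receive ACT if offered it. Let g be the amount, in SD units, by which receivers' untreated outcome is better than non-receivers'. Randomisation gives both arms the same mix. With no treatment effect and receivers' mean set to 0:
- ACT arm after exclusion: mean 0.
- Whole SMC arm: mean −p·g.
- Per-protocol difference: p·g. It is zero only if p or g is zero, and it reverses sign if g is negative.

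**Inputs.** Both p and g are assumptions. The 24% is borrowed from the earlier face-to-face trial and 10% is a lower value for comparison. The gap g is taken as 0.25 and 0.5 SD.

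**Type I error.** The per-protocol SE is √(1/61.6 + 1/((1 − p)·61.6)), which is 0.185 at p = 0.10 and 0.194 at p = 0.24. The two-sided rejection rate under no effect is Φ(pg/SE − 1.96) + Φ(−pg/SE − 1.96).

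| p | g | Bias p·g (SD) | Type I error |
|---|---|---|---|
| 0.10 | 0.25 | 0.025 | 5.2% |
| 0.10 | 0.50 | 0.05 | 5.8% |
| 0.24 | 0.25 | 0.06 | 6.1% |
| 0.24 | 0.50 | 0.12 | 9.5% |

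Simulation with 62 per arm at p = 0.24 and g = 0.5 gave a per-protocol mean of 0.121 with 9.6% rejection, an intention-to-treat rejection of 5.1%, and a complier estimate of −0.002.

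**With a true effect of 0.5 SD in receivers** (p = 0.24, g = 0.5): intention to treat = 0.76 × 0.5 = 0.38; complier estimate = 0.38/0.76 = 0.50; per-protocol = 0.50 + 0.12 = 0.62.

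**Baseline adjustment.** The planned model includes baseline QoL, so the table is before adjustment. Assume a baseline–outcome correlation of 0.6 and write h for the receiver/non-receiver gap already present at baseline. The remaining bias is roughly p(g − 0.6h). At p = 0.24 and g = 0.5:
- h = 0: 0.24 × 0.50 = 0.12, so no reduction.
- h = 0.25: 0.24 × 0.35 = 0.084.
- h = 0.5: 0.24 × 0.20 = 0.048.

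Simulation agrees: about 0.086 SD with 8–9% rejection at h = 0.25, and about 0.05 SD with about 6% at h = 0.5. The complier estimate stays near zero throughout.

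**Precision of the complier estimate.** The intention-to-treat SE is √(2/61.6) = 0.180. The complier SE at p = 0.24 is 0.180/0.76 = 0.237.

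**When the complier estimate is itself biased.** Suppose the 24% classed as non-receivers read some modules and gain 0.25 SD, while compliers gain 0.50. Intention to treat is then 0.76 × 0.50 + 0.24 × 0.25 = 0.44, and the complier estimate is 0.44/0.76 = 0.58, which is 0.08 too high.

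**The case against.** Several points on the other side stand.

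- **The analysis is secondary.** It is one of two sensitivity analyses and would be read beside the intention-to-treat result. A reader might infer that the trial's main conclusion is at risk; it is not.
- **The sentence is unfinished.** It may have been meant to refer to allocated treatment. An SMC participant who starts outside therapy departs from SMC as defined and might then be excluded too. So a claim that exclusions can occur only in the ACT arm is too strong. That case would be contamination rather than non-receipt, though, and excluding it would add a second selection without restoring the randomised comparison.
- **The 24% is not a forecast for this trial.** It comes from a 16-session programme with a travel burden and is cited to justify a brief remote design. A reader might infer that about a quarter of the ACT arm will be dropped; the article does not support that. At 10% non-receipt the illustrated bias is at most 0.05 SD.
- **The gap and its sign are assumed.** A reader might infer that the per-protocol result will exceed the true effect, or favour ACT when there is none. No passage establishes this, and participants who stop because they feel better would push the bias the other way.
- **Baseline adjustment helps**, as shown above, though not where the gap is absent at baseline.
- **The complier analysis is not free of bias.** With a demanding receipt threshold it can err by as much as the per-protocol analysis.

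The exact definition of receipt may properly sit in an analysis plan that is not shown. What remains is that the article commits to exclusion on post-randomisation behaviour. No definition of receipt within that rule makes the comparison randomised.

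**Conclusion.** The point holds as a flaw in a stated sensitivity analysis. Its only named check on departures from randomised treatment compares a selected ACT group with an unselected SMC group, and it also sits awkwardly with the article's own rule that all analyses follow intention to treat. That exclusions fall essentially on the ACT arm is inferred from how SMC and ACT are described, because the sentence itself does not say.

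The size is uncertain and probably modest: 0.025–0.12 SD before adjustment, against a target of 0.5 SD, with type I error of about 5–10%. This rests on assumed non-receipt of 10–24%, an assumed gap of 0.25–0.5 SD, and receivers having the better prognosis.

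**What to change.** - Complete the sentence so that it says what is not received.
- Keep intention to treat as the primary analysis.
- Make a complier average causal effect analysis the main analysis of departures from treatment. Use randomised arm as the instrument for receipt of ACT, with baseline QoL and centre as covariates. Since SMC participants have no planned access to ACT, non-compliance is one-sided and two-stage least squares is enough.
- Fix the definition of receipt before unblinding, and set the threshold low, so that those classed as non-receivers have had little or no exposure and the exclusion restriction is plausible. State that assumption, and the one made about missing outcomes.
- If the per-protocol analysis is kept, report it only as a supplementary, non-randomised comparison.

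The cost is some analysis-plan wording and a few lines of code. Departures are already to be reported, so no new data collection appears necessary. The statistical price is a wider interval (SE about 0.24, against 0.18 for intention to treat, at 24% non-receipt) and an exclusion restriction that partial module use could violate.

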### Outcome measures

The RA blind to participant allocation will be responsible for ensuring outcome measures are completed at 3, 6 and 9 weeks by all participants. The link to the measures will be sent to participants via email. If participants do not complete the questionnaires by the due date, they will be reminded by the RA. All time points will be taken into account during analysis, but the primary efficacy endpoint is the 9-week follow-up.

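### The primary model names only a random intercept, so the 9-week standard error is pooled with weeks 3 and 6 and is right only if variance and correlation are equal across visits

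*Protocol article*

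**What the plan says.** The article makes one visit decisive: "the primary efficacy endpoint is the 9-week follow-up" (Outcome measures). Under Statistical methods the primary analysis uses every follow-up: "Quality of life at all three postrandomisation time points (3, 6 and 9 weeks after randomisation) will be modelled simultaneously using a linear mixed-effects model". The mean structure is flexible over time: it has arm, categorical time and their interaction, so every visit gets its own treatment effect. The other covariates are given as follows: "included in the model will be the baseline level of the QoL score and a stratification indicator variable for centre". Baseline therefore enters once, and no baseline-by-time term is listed.

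The only within-patient term named for this outcome is in the sentence "A random intercept will account for the non-independence of observations across individuals". The paragraph mentions no visit-specific residual variance, unstructured covariance or robust standard error. For the secondary outcomes, measured on the same people at the same visits, the next paragraph says: "Random effects for the intercept and time will be included in the model". No reason is given for the difference. The section sets a two-sided 5% level and allows missing follow-ups under missing at random. The Sample size section expects 20% attrition.

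**The concern.** A random intercept with independent, equal-variance residuals is compound symmetry: a common variance and a common correlation at weeks 3, 6 and 9. The model lets the treatment effect differ by visit but does not let the spread differ. The week-9 contrast is then tested against a variance averaged over three visits, and two of those visits are not the endpoint.

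Correlation with baseline often weakens as time passes. When it does, the variance left after baseline adjustment grows from week 3 to week 9 even if the raw SD stays the same. Averaging then understates the week-9 variance, the confidence interval is too narrow and the test rejects too often. If the spread shrinks over time, the error runs the other way.

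The outcome that decides the trial thus has the more restrictive error model, while the secondary outcomes have a less restrictive one. Missing data add a second route. Under missing at random, observed earlier visits inform the missing week-9 values through the assumed covariance, so a wrong structure could also affect the estimate. That effect has not been quantified here.

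**Working it through.** **The plan's own figures.** The Sample size section states: "This sample size will provide adequate power to detect a standardised mean difference of 0.5 (medium magnitude) in the primary outcome", with 5% significance, 80% power, 20% attrition and 77 per arm.
- Normal approximation: 2 × (1.960 + 0.842)² / 0.5² = 62.8, so 63 per arm; the t-test version is 64.
- 64 × 1.2 = 76.8 gives the stated 77. Dividing 63 by 0.8 gives 79 per arm, or 158 in total, within 3% of 154.
- With 77 × 0.8 = 61.6 completers per arm, power is 79%.

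The sample size is therefore reproduced. It is a two-group calculation that does not use the mixed model, so this point does not touch it.

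**Formula for the week-9 standard error.** Let v₃, v₆ and v₉ be the outcome variances given baseline. With complete data, the random-intercept model uses their mean where v₉ belongs:

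model SE / true SE ≈ √[mean(v₃, v₆, v₉) / v₉]

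two-sided type I error ≈ 2 × [1 − Φ(1.96 × ratio)]

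At constant SD 1 and baseline correlation r, v = 1 − r². The article gives no visit-level SDs or correlations, so every r and SD below is an assumption.

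| Assumed pattern over weeks 3, 6, 9 | v₃, v₆, v₉ | Mean / v₉ | SE ratio | Type I error |
|---|---|---|---|---|
| Equal variance and correlation (r = 0.7) | 0.51, 0.51, 0.51 | 1.000 | 1.00 | 5.0% |
| r = 0.70, 0.65, 0.60, constant SD | 0.510, 0.578, 0.640 | 0.576/0.640 = 0.900 | 0.95 | 6.3% |
| r = 0.70, 0.60, 0.50, constant SD | 0.51, 0.64, 0.75 | 0.633/0.75 = 0.844 | 0.92 | 7.2% |
| r = 0.7 throughout, SD 1, 0.93, 0.86 | 0.510, 0.441, 0.377 | 0.443/0.377 = 1.174 | 1.08 | 3.4% |

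**Simulation.** These runs assumed no true effect, 77 per arm and about 20% missing at week 9. The stated random-intercept model was fitted by REML, with centre left out.
- Compound symmetry true: ratio 1.01, type I error 5.2%.
- r = 0.70, 0.65, 0.60: ratio 0.93, 7.1%. r = 0.7, 0.6, 0.5: ratio 0.90, 7.9% (2000 runs each; Monte Carlo error about 0.6 points).
- Three other patterns of mild decay (0.80/0.70/0.65, 0.75/0.63/0.56 and 0.61/0.55/0.50): ratio 0.92 to 0.95, 6.4% to 7.1%.
- SD falling to 0.86 at equal correlation: ratio 1.08, 3.3%. SD falling to 0.9 in a separate set of runs: ratio 1.04, 4.3%.
- Stronger first-order autoregressive (AR(1)) decay with parameter 0.8: ratio 0.85, 9.7%. With the SD also rising to 1.2 by week 9: ratio 0.80, 12.2%.

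**With the fix.** An unstructured covariance with baseline-by-time gave ratios of 1.00 to 1.03 and type I errors of 4.8% to 5.4% in all four scenarios tried (2000 runs each). When compound symmetry was true, the empirical standard error was 0.1272, against 0.1262 for the random intercept. That is 0.8% larger and within simulation error. Under AR(1) with parameter 0.8 it was smaller, 0.1512 against 0.1559.

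**The case against.** The strongest reply is that a random intercept with categorical time and arm-by-time terms is a recognised trial analysis that gives a separate 9-week effect. The article is a condensed text without its analysis plan. It names the random effect but does not say that residuals are independent and equal in variance, and it excludes neither visit-specific variances nor a robust standard error. The follow-ups span only nine weeks in chronic conditions, with the same questionnaire, so marked changes in spread need not occur. A pattern-mixture sensitivity analysis is already planned for missing outcomes.

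Much of this stands. The equal-variance reading is the usual default but is not written down. Degrees-of-freedom methods and convergence fallbacks belong in the analysis plan, and their absence is no finding. With complete data the point estimate is essentially unaffected. The pattern-mixture analysis addresses missingness but not the pooled standard error.

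The reply does not remove the point. The random intercept is a stated rule for the primary analysis, and the next paragraph states a richer rule for less important outcomes without explanation.

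A reader might go further and infer that the primary standard error is probably too small, that the p-value will be wrong, or that type I error reaches 12%. The article does not support any of these. It reports no SDs by visit and no between-visit correlations. The same calculations give a correct test under compound symmetry and a conservative one when variance falls. The 12% case needs strong decay of correlation together with a clear rise in SD.

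**Conclusion.** The point holds in conditional form. As written, with ordinary residuals, the primary model ties the week-9 standard error to weeks 3 and 6, and the test keeps its 5% level only if variance after baseline adjustment and correlation are equal over the visits.

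Under mild decay of correlation with baseline (from 0.70 to between 0.60 and 0.50, constant SD), the standard error is about 5-10% too small and type I error is about 6-8%. Under falling variance, type I error is about 3-4%. Weakening correlation is common in repeated questionnaires, which makes the first direction plausible, but neither size nor direction can be established from the article. The sample size is unaffected. This is an inexpensive improvement to the primary model and an unexplained inconsistency with the secondary models. It is not a flaw that invalidates the design.

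**What to change.** In the primary model, replace the random intercept with an unstructured residual covariance over weeks 3, 6 and 9, and add a baseline-by-time term. Keep arm, categorical time, arm-by-time, baseline and centre. If the random intercept is retained, at least pair it with a robust standard error. That repairs the week-9 standard error but leaves the handling of missing visits dependent on the assumed covariance. If neither change is wanted, state why the primary outcome has a simpler structure than the secondary outcomes. Settle this before database lock.

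The cost is a change of wording and a few parameters: an unstructured 3 × 3 covariance has 3 variances and 3 covariances, six in all against two for the random-intercept model, with 154 participants planned. No new data are needed. If compound symmetry is true, the loss of precision is negligible.
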